#### Exclusion criteria

2.2.2

(1) Pregnancy or lactation.(2) Individuals who do not respond to acupuncture stimulation.(3) Individuals with claustrophobia.(4) Those with metallic implants or other contraindications for MRI.

#### Withdrawal criteria during the study

2.2.3

(1) Participants who fail to comply with the study procedures, thereby compromising data quality.(2) Those who experience severe adverse events or emergencies during the trial.(3) Participants unable to complete the study as scheduled.(4) Those exhibiting excessive head motion during MRI scanning, leading to unusable data.(5) Participants who receive other acupuncture treatments during the trial period.

### Sample size

2.3

Currently, there are no standardized criteria for determining sample sizes in MRI studies, as they are often constrained by practical considerations such as scanning time and cost. Based on an efficiency analysis of sample size estimation in MRI research, a previous study indicated that approximately 12 participants are required to achieve 80% power at the single-voxel level for typical activation effects (19). In line with this reference and considering the study design, we set a sample size of 30 participants per acupuncture point. Each volunteer will undergo both verum and sham acupuncture at the same acupoint, resulting in a total of 210 experimental sessions. To account for potential data loss due to head motion or participant dropout, we plan to enroll a total of 250 subjects.

### Randomization, allocation concealment, and blinding

2.4

In this study, participants will be randomly assigned to one of the seven acupoint groups. The randomization sequence is generated using SPSS 26.0 software, and the allocation scheme is concealed using opaque sealed envelopes. Upon participant enrollment, the allocation will be revealed by sequentially opening the envelopes to determine the assigned acupoint for acupuncture. The blinding procedure involves three aspects: first, participants are blinded to the specific acupoints used in the trial; they are only informed that the acupoints are located in the distal limbs. Second, radiologists, due to their professional constraints, are unaware of the specific acupoints and their significance, ensuring the objectivity of the scanning process. Third, image processors are blinded to the participants’ group assignments, ensuring the objectivity of the image processing.

### Intervention

2.5

Based on a comprehensive review of fMRI studies exploring acupuncture mechanisms and clinical consensus on frequently used acupoints, this study selects the following acupoints: LI4 (Hegu), PC6 (Neiguan), ST36 (Zusanli), SP6 (Sanyinjiao), GB34 (Yanglingquan), KI3 (Taixi), and LR3 (Taichong) (Table 1 and Figure 3). These acupoints frequently employed in clinical practice to regulate the flow of Qi and blood, address imbalances in multiple organ systems (Zang-fu), and promote overall homeostasis. All acupoint localizations strictly adhere to the WHO Standard Acupuncture Point Locations in the Western Pacific Region (20).

**Table 1 tab1:** Locations of acupoints.

Acupoints	Locations	Insert depth
Hegu (LI4) (unilateral)	On the dorsum of the hand, radial to the midpoint of the second metacarpal bone	0.5–1 cun
Neiguan (PC6) (unilateral)	On the anterior aspect of the forearm, between the tendons of the palmaris longus and the flexor carpi radialis, 2 B-cun proximal to the palmar wrist crease	0.5–1 cun
Zusanli (ST36) (unilateral)	On the anterior aspect of the leg, on the line connecting ST35 with ST41, 3 B-cun inferior to ST35	1–2 cun
Sanyinjiao (SP6) (unilateral)	On the tibial aspect of the leg, posterior to the medial border of the tibia, 3 B-cun superior to the prominence of the medial malleolus	1–1.5 cun
Yanglingquan (GB34) (unilateral)	On the fibular aspect of the leg, in the depression anterior and distal to the head of the fibula	1–1.5 cun
Taixi (KI3) (unilateral)	On the posteromedial aspect of the ankle, in the depression between the prominence of the medial malleolus and the calcaneal tendon	0.5–0.8 cun
Taichong (LR3) (unilateral)	On the dorsum of the foot, between the first and second metatarsal bones, in the depression distal to the junction of the bases of the two bones, over the dorsalis pedis artery	0.5–0.8 cun

*B-cun: *proportional bone (skeletal) cun.

**Figure 3 fig3:**
[figure not shown]
Location of acupoints and non-acupoints in the trial.

#### Verum acupuncture group

2.5.1

Following skin disinfection, an opaque, non-metallic sponge pad will be positioned on the skin surrounding the target area. Non-magnetic acupuncture needles (Suzhou Acupuncture & Moxibustion Appliance Co., Ltd., China; 0.25 × 40 mm) will be inserted to 2 cm deep into the designated acupoints on the right limbs (Table 1). After Deqi (A special sensation of acupuncture characterized by pain, soreness, distension, heaviness, or numbness), twisting (90–180°, 60–90 times/min), and lifting-thrusting (0.3–0.5 cm, 60–90 times/min) were performed for 1 min. During task-based fMRI scanning, the same twisting manipulation will be performed for 60 s at 60-s intervals (synchronized with scan initiation), continuing until completion of the 6-min 6-s protocol, followed by needle removal.

#### Sham acupuncture group

2.5.2

Non-acupoints are localized at 1.5 cm lateral to the corresponding verum acupoints (Table 1), outside meridian trajectories and neurovascular bundles, avoiding tender points and hair follicles (Figure 3). Identical opaque, non-metallic sponge pads, as used in the verum group, will be placed on the skin surrounding the target area after disinfection. Blunt-tipped placebo needles (Suzhou Acupuncture & Moxibustion Appliance Co., Ltd., China; 0.25 × 30 mm) will be vertically placed on the skin surface without penetration, maintaining slight tactile pressure. Hence, the Deqi experience of the participants will not be overemphasized. Except locations of acupoints and needle penetration, the manipulation procedures and course will be the same with the verum acupuncture group (Figure 4).

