To address these limitations, the present study employs a rigorous, single-acupoint design under a well-controlled, task-based fMRI paradigm. We focus on a therapeutically significant and commonly used acupoint to precisely investigate its distinct impact on functional brain network dynamics. Our objectives are twofold: (1) to isolate the specific central effects of a defined acupoint from non-specific responses using a robust sham-control design, and (2) to interpret these findings within the established framework of CNS network modulation, thereby contributing to a more precise understanding of acupuncture’s neural mechanisms and its potential applications in cognitive regulation.

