#### Common brain effects

3.1.1

Both verum and sham acupuncture may commonly activate a brain network involving the anterior cingulate cortex, anterior insula, primary/secondary somatosensory cortices, and prefrontal cortex. This network is responsible for processing stimulus salience, bodily sensations, and cognitive appraisal, reflecting the non-specific effects of acupuncture. That is, this brain activity largely stems from shared components such as attention, sensation, and expectation elicited by the skin penetration itself, overlapping with the neural substrates of placebo effects.

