### Blinding assessment and placebo effects

3.5

The blinding assessment may show that a portion of participants cannot accurately distinguish between verum and sham acupuncture, with a potentially high proportion selecting “uncertain.”

If the subjective guesses between groups do not differ significantly, then the differences in brain responses are more likely attributable to the biological effects of acupuncture itself rather than participant expectation. This would enhance the credibility of the findings. Even if placebo effects are present, this study is well-designed to dissociate them (common effects) from the specific effects (differential effects) using neuroimaging.

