Currently, there are two major paradigms for task-based fMRI study: non-repeated event-related (NRER) design and block design. NRER designs effectively capture transient neural responses to discrete stimuli (e.g., instantaneous needle insertion) (47). In contrast, our block design paradigm better reflects real-world clinical acupuncture practice which comprises four sequential phases: needle insertion, needle manipulations (lifting-thrusting and rotating) to elicit Deqi, needle retention and needle withdrawal. Acupuncture elicits prolonged neural and hemodynamic responses rather than transient bursts of activity. Block design, with its alternating periods of stimulation and rest (e.g., 60 s needle manipulation followed by 60 s rest), optimally captures these sustained effects. Furthermore, as the most commonly applied and the most efficient paradigm (46, 47), block design has the advantages of a relatively large blood oxygen level dependent (BOLD) signal change relative to baseline (48), superior signal-to-noise ratio (SNR) and increased statistical power (47, 49).

However, there are some limitations in this study. Firstly, due to resource constraints, this study will be unable to encompass all acupoints. Future work will be needed to construct a comprehensive brain mapping encompassing all acupoints to better inform clinical practice. Secondly, considering the characteristics of acupuncture, it is difficult to design a practitioner-blinded trial. Thirdly, the study will be limited to manual acupuncture, which may introduce variability due to subtle differences in needle manipulation techniques. Furthermore, different acupuncture modalities (e.g., electroacupuncture vs. manual acupuncture) may induce different effects (46, 50, 51). Future studies should compare outcomes across different acupuncture modalities to determine modality-specific neural correlates. Finally, although a sham acupuncture control will be employed, this approach may not eliminate the influence of placebo effects inherent in acupuncture trials.

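### The verum-sham contrast varies location and penetration together, so it cannot isolate an effect of the acupoint, although the objective and parts of the interpretation read as if it could

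*Protocol article*

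**What the plan says.** Section 2.5.1 (Verum acupuncture group): needles "will be inserted to 2 cm deep into the designated acupoints on the right limbs". The order of manipulation is "After Deqi (A special sensation of acupuncture characterized by pain, soreness, distension, heaviness, or numbness), twisting" and then lifting-thrusting.

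Section 2.5.2 (Sham acupuncture group): "Non-acupoints are localized at 1.5 cm lateral to the corresponding verum acupoints". The sham needle is blunt, stays on the skin surface and exerts light pressure, and Deqi is not emphasised. The section then lists what differs: "Except locations of acupoints and needle penetration, the manipulation procedures and course will be the same with the verum acupuncture group".

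The interpretation is set out in four other places:

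- The Introduction gives the first objective as "to isolate the specific central effects of a defined acupoint from non-specific responses using a robust sham-control design".
- Section 2.7.3 describes the paired verum-sham t-test as a comparison of acupoints with non-acupoints.
- Section 3.1.1 explains activation common to verum and sham by attention, sensation and "expectation elicited by the skin penetration itself".
- Section 3.5 states that, even if placebo effects are present, "this study is well-designed to dissociate them (common effects) from the specific effects (differential effects) using neuroimaging".

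The limitations in the Discussion say of the sham control that "this approach may not eliminate the influence of placebo effects inherent in acupuncture trials". They do not mention that location and penetration change together.

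**The concern.** A verum-sham difference in brain response could come from where the needle is, from the fact that it pierces tissue and produces Deqi, or from both. The design offers no way to tell these apart. If needle location made no difference at all, penetration with Deqi could still produce a clear differential map, and the wording of the first objective and Section 2.7.3 would invite readers to credit it to the acupoint. The protocol article itself supplies a plausible source of such a difference: Section 3.3 expects the intensity of Deqi sensations to correlate with insula and anterior cingulate activation.

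Section 3.1.1 errs in the opposite direction. It puts penetration among the components shared by both arms, when only verum has it. Touch, attention and expectation would then be described as consequences of penetration, while the real penetration effect sits in the differential map under another name.

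**Working it through.** The plan states no figure on this point, so there is none to reproduce. The check is one of identifiability, followed by an illustration.

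**1. What each condition contains (Sections 2.5.1 and 2.5.2)**

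| Condition | At acupoint | Penetrating | Deqi |
|---|---|---|---|
| Verum | 1 | 1 | 1 (manipulation follows it) |
| Sham | 0 | 0 | 0 (not emphasised) |

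Coding sham Deqi as 0 is a simplification, because the text does not say that it is absent. Deqi is a response to needling rather than an assigned factor, so step 2 is also done without it.

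**2. What can be estimated**

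With an intercept, location L, penetration P and Deqi D, the design rows are (1,1,1,1) for verum and (1,0,0,0) for sham. The rank is 2 for 4 parameters. Folding Deqi into penetration leaves (1,1,1) and (1,0,0): rank 2 for 3 parameters. Either way the only estimable contrast is

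verum − sham = L + P (+ D).

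A location effect of size x with no penetration effect gives the same expected data as a penetration effect of size x with no location effect. More participants sharpen the estimate of the sum and do not split it.

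For comparison, adding a penetrating non-acupoint condition, row (1,0,1), gives rank 3 for intercept, L and P, so both become estimable if they are additive. A full 2×2 of location by penetration gives rank 4, including the interaction. The plan has neither condition.

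**3. Sections 3.1.1 and 2.5.2 side by side**

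Section 2.5.2 says the sham does not pierce the skin. Section 3.1.1 attributes activation common to verum and sham to skin penetration. Both cannot be right. A component present in one arm only can enter the difference and cannot explain what the arms share.

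**4. Illustration of the risk**

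Inputs: n = 30 per acupoint (Section 2.3) and a voxel-wise threshold of p < 0.005 (Section 2.7.3). The standardised paired effect dz of penetration with Deqi is my assumption, because the document gives none. The location effect is set to zero. The test is a two-sided paired t-test with 29 degrees of freedom and noncentrality dz × √30, which is 0.5 × 5.477 = 2.74 at dz = 0.5 and 0.8 × 5.477 = 4.38 at dz = 0.8.

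| Assumed dz | P(significant), p < 0.005 uncorrected | P(significant), p < 0.05 |
|---|---|---|
| 0.2 | 0.04 | 0.19 |
| 0.5 | 0.40 | 0.75 |
| 0.8 | 0.90 | 0.99 |
| 1.0 | 0.99 | >0.99 |

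The middle column is closer to the plan's criterion. It still ignores the cluster-level correction, so it is not the probability of a reported cluster.

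**The case against.** The strongest reply is that a non-penetrating sham at a nearby non-acupoint is an openly disclosed choice and a legitimate way to ask whether needling does more than touch. That stands, and the sham need not change.

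A reader might infer that the plan lays down a rule by which every verum-sham difference counts as acupoint-specific. No passage says this. Section 3.5 speaks of specific effects as opposed to placebo, and just before that it refers to biological effects of acupuncture, which is compatible with a needling effect. That earlier sentence is hedged and conditional on participants' guesses not differing. The first objective can also be read mildly: the Introduction complains of studies that combine several points and confuse specific with placebo responses, so a defined acupoint may simply mean one point rather than many. These readings soften the charge but do not remove it. The objective still ties the result to the acupoint, Section 2.7.3 still labels the test by location, and the dissociation sentence in Section 3.5 carries no condition of its own. That sentence also sits badly with the limitation in the Discussion.

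A reader might also infer that comparing verum minus sham between the seven acupoints solves the problem because all seven verum conditions penetrate. The Abstract and Discussion do use acupoint specificity in this between-point sense. But penetration cancels only if its effect is equal at every site. The sites span hand, forearm, leg, ankle and foot, and Table 1 lists depths from 0.5–0.8 to 1–2 cun. Those depths must in turn be reconciled with the single 2 cm in Section 2.5.1.

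Finally, Deqi is not an assigned third factor. It follows from needling and is measured by C-MMASS. I therefore treat it as part of the penetration component.

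**Conclusion.** The point holds as one of identification and wording. The verum-sham contrast estimates one combined effect, and the document does not support attributing it to acupoint location. Section 3.1.1 contradicts Section 2.5.2 on penetration, and the limitations omit the confound. These conclusions follow from the described conditions alone and need no assumed effect size.

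The illustrative probabilities of 0.40 to 0.90 rest on an assumed dz of 0.5 to 0.8, a zero location effect, n = 30 and an uncorrected single-voxel threshold. A reader might take the 0.75 to 0.99 at the 5% level as the trial's risk of a false claim. The plan does not test at that level, and even the stricter figures say only how often the combined effect would be noticed.

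The correction changes what the trial may conclude. It does not call for redesign, and allocation and data collection are unaffected. It should be made before results are interpreted, but it is not a defect that invalidates the trial.

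**What to change.** Keep the sham and change four pieces of text.

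1. **Introduction (first objective) and Section 2.7.3.** State that verum minus sham estimates the combined effect of penetrating needling with Deqi at the acupoint versus non-penetrating touch at a nearby non-acupoint, and that it will not be attributed to location.
2. **Section 3.1.1.** Reconcile with Section 2.5.2: take penetration out of the explanation of shared effects and name it as a component of the differential effects in Section 3.1.2.
3. **Section 3.5 and the limitations in the Discussion.** Delete or limit the claim that common and differential effects dissociate placebo from specific effects. Add the confounding of location with penetration to the limitations.
4. **Any use of acupoint-specific for differences between acupoints in verum minus sham.** State that this assumes an equal penetration effect at all sites and that such differences may also reflect body region and needling depth.

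The cost is rewording and a less favourable claim. No arm, scan, participant or test is added. An effect of location alone would need a further condition, which this correction does not ask for.

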**Figure 4 fig4:**
[figure not shown]
Verum and sham acupuncture.

#### Acupuncturist qualification

2.5.3

To ensure consistency, licensed acupuncturist will be trained to conduct the acupuncture operations.

### Outcome measurements

2.6

#### Demographic and basic clinical information collection

2.6.1

The demographic information (age, gender, education, marital status and occupation) and time of enrollment will be obtained at baseline.

#### MRI scanning protocol

2.6.2

The fMRI data will be acquired with the Siemens Prisma 3.0T MRI (Siemens, Munich, Germany) at the Shenzhen Traditional Chinese Medicine Hospital, Shenzhen, China. High-resolution T1-weighted structural images will be acquired using a magnetization-prepared rapid gradient-echo (MPRAGE) sequence with the following parameters: repetition time (TR) = 2,200 ms, echo time (TE) = 2.45 ms, field of view (FOV) = 256 mm × 256 mm, isotropic voxel resolution = 1 × 1 × 1 mm^3^, 175 slices with no interslice gap, and a flip angle (FA) of 8°. For resting-state and task-based functional scans, the parameters will be as follows: TR = 2,000 ms, TE = 30 ms, 37 slices, in-plane resolution = 64 × 64, voxel resolution = 3.75 × 3.75 × 4 mm^3^, and 240 volumes acquired per run. Before the scanning session, participants will be positioned supine with their heads immobilized using a pillow. They will be instructed to keep their eyes closed, remain relaxed, avoid deliberate mental activity, and breathe naturally. Foam earplugs are provided to minimize scanner noise. Scanning commences after participants have acclimated to the environment.

Both verum and sham acupuncture protocols will follow the procedure below (Figure 2). After 20 min of quiet rest, the subject will first undergo a 14-s locator scan to determine the imaging range. This will be followed by a 4-min and 39-s 3D high-resolution T1-weighted imaging sequence to acquire anatomical structural information. A pre-acupuncture resting-state fMRI scan lasting 6 min and 6 s will then be performed. Subsequently, a licensed acupuncturist will enter the MRI scanning room to administer acupuncture on the right limb using a block paradigm: three 60-s cycles of twisting needle manipulation will alternate with three 60-s cycles of needle-retaining baseline states. Concurrently, task-based fMRI scanning will be conducted for 6 min and 6 s. Following needle removal, a 6-min and 6-s post-acupuncture resting-state fMRI scan will be acquired.

#### Blinding assessment

2.6.3

When recruiting and screening eligible participants, subjects will be informed that they will receive both verum and sham acupuncture stimulation while the orders of presentation remain blinded to them. Following the completion of two fMRI scanning sessions, participants will be asked to guess the type of acupuncture they received during each session to assess the blinding effectiveness. The question posed to participants will be: “Which type of acupuncture do you believe you received during the two sessions?” Participants will be provided with three response options: traditional acupuncture, sham acupuncture, or uncertain.

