### Study design

2.1

This prospective, single-center, randomized, single-blind, placebo-controlled study will enroll 250 healthy participants. Participants will undergo acupuncture in separate sessions at one of seven predefined acupoints (verum acupuncture) and its corresponding non-acupoint (sham acupuncture), with a 1-week interval between sessions (18) (Figure 1). All participants will undergo two identical fMRI scanning sessions, separated by a 1-week interval, which corresponds to the washout period between the two acupuncture interventions. Each session will include resting-state fMRI scans before and after acupuncture, as well as task-based fMRI scans during acupuncture (Figure 2). The sequence of verum and sham protocols will be randomized across all fMRI runs, and the order of presentation will be counterbalanced across subjects (18).

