#### Deqi sensation assessment

2.6.4

Following the completion of both trials, participants will be assessed for the types and intensity of Deqi sensations using the Modified Massachusetts General Hospital Acupuncture Sensation Scale-Chinese version (C-MMASS) (21). The C-MMASS evaluates 12 specific types of sensations: soreness, pain, pressure, heaviness, distension, tingling, numbness, dull ache, warmth, cold, throbbing, and other sensations. The intensity of each sensation will be rated on a scale from 0 to 10, where 0 indicates no sensation, 1–3 represents mild intensity, 4–6 moderate intensity, 7–9 severe intensity, and 10 signifies the maximum tolerable intensity.

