### Correlation between subjective sensations (Deqi—C-MMASS) and objective brain activity

3.3

The intensity and multidimensional characteristics of the “Deqi” sensation will correlate strongly with specific patterns of brain activity. The composite intensity of sensations like soreness, numbness, distension, and heaviness may positively correlate with activation intensity in the insula and ACC.

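### The blinding question contradicts its own per-session purpose, and both it and (on the natural reading) the Deqi rating are taken only after the second session

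*Protocol article*

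**What the plan says.** All four places are in the protocol article.

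- **Section 2.6.3, what participants know:** "subjects will be informed that they will receive both verum and sham acupuncture stimulation while the orders of presentation remain blinded to them".
- **Section 2.6.3, timing and unit:** "Following the completion of two fMRI scanning sessions, participants will be asked to guess the type of acupuncture they received during each session".
- **Section 2.6.3, the item:** "Which type of acupuncture do you believe you received during the two sessions". The answers allowed are: "Participants will be provided with three response options: traditional acupuncture, sham acupuncture, or uncertain".
- **Section 2.6.4, Deqi (C-MMASS):** "Following the completion of both trials, participants will be assessed for the types and intensity of Deqi sensations". No rating at the end of the first session is described.
- **Section 2.1, spacing:** "All participants will undergo two identical fMRI scanning sessions, separated by a 1-week interval". The order of verum and sham is randomized and counterbalanced.

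Two later sections lean on these data. Section 3.3 expects that Deqi intensity "will correlate strongly with specific patterns of brain activity". Section 3.5 reads the guesses as follows: "If the subjective guesses between groups do not differ significantly, then the differences in brain responses are more likely attributable to the biological effects". The explanation it thereby sets aside is expectation.

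**The concern.** The stated purpose is a guess per session, but the fixed wording asks for one type across two sessions. The true answer for everyone is one of each, and no option says that. Timing is a separate problem. By the time the question is put, the participant has felt both a needle inserted to 2 cm and manipulated (Section 2.5.1) and a blunt tip resting on the skin (Section 2.5.2). The answer therefore reflects a comparison of the two, whereas Section 3.5 needs to know what was believed while each scan was running. The Deqi rating has a related weakness if session 1 is rated only after session 2.

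At stake are the evidence that the sham was credible and the Deqi-brain correlation. Neither can be repaired in analysis: once session 2 has taken place, belief and fresh sensation from session 1 cannot be recovered.

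**Working it through.** The plan gives no figure on this point to reproduce. The check is a scoring exercise on the item, followed by two short calculations.

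**1. One answer covering both sessions (the literal wording).** Let *a* be the share answering traditional, *b* the share answering sham, and the rest uncertain. Each person had one session of each type, so the same answer is scored against both.

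- Blinding index (share right minus share wrong): verum session = *a* − *b*; sham session = *b* − *a*; mean = 0.
- Illustration (assumed shares): *a* = 0.8, *b* = 0.1 gives +0.7 and −0.7, mean 0. With *a* = 0.5, *b* = 0.3 it is +0.2 and −0.2, mean 0.
- Correct among committed answers, over the two sessions: 1 of 2 = 50%, always.
- Difference between conditions in the share guessing traditional: *a* − *a* = 0, always.

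The condition in Section 3.5 is then met by construction, whatever the true unblinding. (I take its groups to be the verum and sham conditions.)

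**2. One answer per session (the stated intent).** There are 3 × 3 = 9 possible answer pairs in place of 3 single answers, and the index can be scored. Complete unblinding gives 1 − 0 = 1.0; 80% right and 10% wrong gives 0.7; 40% and 40% gives 0 (assumed shares). Two limits remain. Participants know they get one of each, so the two guesses are strongly dependent. Both guesses also come after both stimuli, so they measure whether the sessions can be told apart afterwards.

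**3. Deqi recall.** On the natural reading of Section 2.6.4, the lag is about 7 days for session 1 and about 0 for session 2. With counterbalanced order, about half the ratings in each condition are late. The documents give no reliability, so assume *r* = 0.6 for recalled ratings (range 0.5 to 0.8), error-free fresh ratings and equal true variance (set to 1).

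- Error variance of a recalled rating = 1/*r* − 1; averaged over the half-and-half mix = (1/*r* − 1)/2.
- Pooled reliability = 1 / [1 + (1/*r* − 1)/2].
- Observed correlation = 0.50 × √(pooled reliability).

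| *r* | Mean error variance | Pooled reliability | 0.50 becomes |
|---|---|---|---|
| 0.5 | 0.500 | 0.667 | 0.41 |
| 0.6 | 0.333 | 0.750 | 0.43 |
| 0.8 | 0.125 | 0.889 | 0.47 |

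**4. Precision of percent correct.** Half-width of the 95% CI at 50% correct = 1.96 × √(0.25/*n*). The planned evaluable number is 7 × 30 = 210.

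- One acupoint, *n* = 30: 0.179, about ±18 points.
- All acupoints, *n* = 210: 0.068, about ±7 points.
- Session-1 guesses split by condition, *n* about 210/2 = 105: 0.096, about ±10 points.

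**The case against.** The strongest reply is that Section 2.6.3 says in plain words that the guess concerns each session. A sensible interviewer would put the question twice, and it could then be scored. That stands. A reader might infer from the question alone that session-level blinding can never be scored; the preceding sentence does not support this. Nor is the second guess fully determined by the first, because uncertain is an option and nothing forces consistent answers.

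On Deqi, the phrase about both trials could mean after each of the two trials. That is possible, though less natural. A reader might also infer that late recall biases verum against sham. Counterbalancing in Section 2.1 spreads the lag over both conditions, so the expected effect is mainly noise. Likewise, attenuating every rating (0.50 × √0.6 = 0.39) would overstate the loss, because only about half the ratings are recalled.

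On inference, Section 3.5 is a hedged remark within anticipated results, not a formal decision rule, and the Discussion concedes that the sham may not remove placebo influence. The primary outcomes are fMRI measures, and the imaging analysis in Section 2.7.3 uses neither the guess nor the C-MMASS. These points bear on severity. They do not resolve the contradiction in wording, and they do not make a guess given after session 2 evidence of belief during session 1.

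**Conclusion.** The concern holds in a limited form. Section 2.6.3 contradicts itself. On the literal single-answer reading the item carries no information on blinding; on the per-session reading it can be scored but measures after-the-fact discrimination. This part rests on the article's wording alone and needs no numerical assumption.

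The Deqi part rests on the natural reading of Section 2.6.4. Its size is illustrative: a true 0.50 seen as about 0.43 (0.41 to 0.47), under the assumed reliabilities and an even split of orders. It does not establish a verum-sham bias.

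A non-significant difference in guesses is weak evidence of blinding on either reading. On the literal one it is automatic; on the other, the interval is wide within one acupoint (about ±18 points) and moderate when pooled (about ±7). This should be fixed before data collection, but it touches supporting measures and does not undermine the primary fMRI outcomes.

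**What to change.** 1. Give the C-MMASS and the guess at the end of each session, after the post-acupuncture resting scan.
2. Reword the item to: *Which type of acupuncture do you believe you received in this session?* Keep the same three options.
3. Name the session-1 guess as the main blinding measure, since it precedes any comparison of the two stimuli.
4. Report percent correct or a blinding index by condition with a 95% CI, pooled over acupoints first.
5. In Section 3.5, do not take a non-significant difference in guesses as evidence that blinding held; interpret the interval.
6. If Section 2.6.4 already means a rating after each session, say so.

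The cost is two short questionnaires at visits that already take place. The downside is that asking after session 1 may draw attention to sensation in session 2, possibly not equally in the two orders. This can be acknowledged and examined by order.
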